# Effectiveness of a 6-week specific rehabilitation program combining education and exercises on walking capacity in patients with lumbar spinal stenosis with neurogenic claudication: a randomized controlled clinical trial protocol

**DOI:** 10.1186/s13063-022-07011-3

**Published:** 2022-12-27

**Keywords:** Neurogenic claudication, Walking capacity, Exercises, Education, Spinal stenosis, Randomized controlled trial

## Abstract

**Background:**

Lumbar spinal stenosis (LSS) causing neurogenic claudication (NC) is a leading cause of disability which is intimately related to a decrease in walking capacity. Walking limitation has negative physical and mental impacts on patients. Recent guidelines recommend the use of conservative treatment options such as exercises before considering surgery. Unfortunately, dedicated healthcare resources for the conservative management of patients with LSS causing NC are uncommon. Thus, it is important to develop accessible and specific rehabilitation programs aimed at improving patients’ self-management, especially with regard to walking capacity. The aim of this study is to evaluate the effectiveness of a 6-week specific rehabilitation program combining education and exercises on walking capacity in patients with LSS causing NC.

**Methods/design:**

This is a prospective randomized controlled parallel-group clinical trial. Sixty-six patients with LSS causing NC will be recruited from identified clinics and local advertisements. The intervention group will receive standardized education and specific exercises while the control group will only receive a standardized education. The program in both groups will last for 6 weeks with 5 evaluation time points (baseline, week 2, week 4, week 6, and week 12). The primary outcome will be walking capacity measured with the Self-Paced Walking Test, and the secondary outcomes will be back and leg pain intensity, LSS-related disability, self-efficacy, level of physical activity, anxiety, depression, gait pattern characteristics, balance, and global perceived change.

**Discussion:**

This study will assess the effectiveness of a 6-week specific rehabilitation program combining education and exercises on walking capacity in patients with LSS causing NC. By measuring objective gait pattern characteristics, the study will also provide new information about the impact of NC on gait pattern that could eventually improve the evaluation and the management of LSS.

**Trial registration:**

ClinicalTrials.gov NCT05513326. Registered on August 22, 2022

**Supplementary Information:**

The online version contains supplementary material available at 10.1186/s13063-022-07011-3.

## Background

Neurogenic claudication (NC) is a clinical syndrome recognized as the hallmark of symptomatic lumbar spinal stenosis (LSS) [1], a degenerative musculoskeletal condition caused by age-related changes in the lower spine and defined as the narrowing of the spinal canal or intervertebral foramina [2, 3]. Neurogenic claudication is characterized by bilateral or unilateral buttock, thigh or leg pain, and discomfort such as numbness, tingling, and weakness [4–7]. These symptoms are exacerbated by prolonged standing or walking, and they are temporarily relieved by sitting and bending forward [1, 6]. Because of its symptomatology, especially during daily activities that require walking, NC represents one of the leading causes of pain and disability in the elderly [8].

Over the past years, decreased walking capacity in patients with LSS causing NC, measured in time or distance, has been well documented using objective walking tests (treadmill and self-paced walking tests) [9, 10]. Moreover, a recent systematic scoping review reported that walking capacity was negatively associated with pain outcomes and disability [11]. In addition, greater disability scores were negatively associated with walking speed and stride length, two important gait pattern characteristics of LSS [11]. Patients consider walking capacity and pain to be the most bothersome consequences of NC. They also report that decreased walking capacity is responsible for disrupting their daily life activities (e.g., walking, social activities, household activities, sleeping, and lifting) [12]. Furthermore, the decline in walking capacity due to NC is reflected in an increase in inactivity. Adoption of such a sedentary lifestyle contributes to a decline in quality of life especially with respect to physical status [13, 14]. Previous studies showed that patients with LSS causing NC are less active than the general population over the age of 60 and individuals with hip or knee osteoarthritis, with approximately 82% of their time spent in sedentary behavior [13–15].

Walking limitations related to LSS causing NC do not only affect patients physically. When asked about their well-being and psychological state, most patients report that they feel sad, discouraged, and/or anxious and that they lost interest in doing certain activities because of their condition [12]. However, there are many different ways to assess psychological factors including anxiety and depression in both clinical and research settings. Due to the lack of standardization regarding the assessment of psychological factors, the association between walking capacity and psychological factors in patients with LSS causing NC remains uncertain [11].

Walking limitations and pain related to NC are central to the management of LSS [1, 12, 16]. Several therapeutic options are available for patients with LSS causing NC including conservative approaches and surgical options. According to recent practice guidelines, surgical options should only be considered when less-invasive treatments such as manual therapy, physiotherapy, exercises, and injections have failed to improve symptoms [17]. Having additional resources such as exercises and education in patients’ healthcare trajectories could help them to at least maintain their functional capacities. Furthermore, underlying medical conditions may limit surgical options in this population. To date, dedicated programs providing active treatments such as exercises to patients with LSS causing NC are scarce. Furthermore, the often protracted delay between diagnosis and eventual surgery may be an opportunity to help patients improve both their pre- and post-surgical functional capacities.

Neurogenic claudication related to LSS can be experienced differently over time and between patients, especially regarding leg pain intensity, time to first symptoms when walking, and total walking time. Knowing that there are currently no specific resources to guide active treatment such as exercises for patients with LSS, identifying and developing specific and flexible rehabilitation programs to help patients to maintain or improve their walking capacity would address an important knowledge gap. Such a program would offer an additional access to healthcare during patients’ care trajectories in addition to offering a chance for patients to self-manage their condition over time. This new opportunity should help them strengthen their self-efficacy during daily living.

Bove and colleagues reported that patients value individual sessions focused on their specific impairments and limitations as well as specific tips on self-management strategies [18]. In the last few years, RCTs involving patients with LSS causing NC were designed to include education as part of the intervention [19–22]. However, the authors did not describe in detail the content of the education program (i.e., daily living tips to limit pain, information regarding walking and sleeping) nor how it was delivered during the study (e.g., frequency, duration, delivery methods such as individual session or information flyers) making the replication of those studies difficult.

The aim of the proposed protocol is to evaluate the effectiveness of a 6-week specific rehabilitation program combining education and exercises on walking capacity in patients with LSS causing NC. It is hypothesized that a 6-week specific rehabilitation program combining exercises and education will have a superior effect on walking capacity than education alone.

## Methods/design

### Study design

The proposed study is a prospective randomized controlled parallel-group clinical trial (RCT) that aims to evaluate the superior effect of a 6-week specific rehabilitation program combining exercises and education compared to education alone (see Fig. 1). In this RCT, participants with LSS causing NC will be allocated to either the intervention group (LSS group) or the control group. All proposed methods are in accordance with the CONSORT statement which provides relevant guidelines and regulations for RCTs [23]. The study protocol is written in conformity with the Standard Protocol Items: Recommendations for Interventional Trials (SPIRIT) statement [24] and has been registered on ClinicalTrials.gov (NCT05513326) on August 22, 2022.

**Fig. 1 Fig1:**
[figure not shown]
Study timeline. LSS = lumbar spinal stenosis, NC = neurogenic claudication

### Recruitment

Potential participants will be identified by neurosurgeons and chiropractors from collaborating clinics during regular scheduled appointments or by advertising in the local newspapers or via social media. Both recruitment strategies (pamphlets given by clinicians or local publicity) will include information regarding the study objectives, patient implication, and contact information of the trial coordinator. If interested, participants will be screened for eligibility criteria over the phone, and then an assessment date will be set. Collaborating clinics are located in Trois-Rivières (Québec, Canada) and refer to the chiropractic university teaching clinic and to the regional hospital neurosurgery outpatient clinic.

#### Eligibility criteria

To be eligible, participants must meet the following inclusion criteria: (1) being at least 50 years old; (2) having a degenerative central LSS alone or in combination with other LSS types (e.g., foraminal, lateral recess) and/or a spondylolisthesis affecting one or multiple vertebral levels, confirmed by clinical history, physical examination, and proper imaging (MRI and/or CT scan); (3) having NC associated with LSS; (4) with a duration of signs and symptoms of at least 3 months; (5) being able to walk at least 20 m without walking aid, but not being able to walk continuously for 30 min; (6) being willing to attend 3 intervention sessions per week over a period of 6 weeks; (7) being able to speak and understand French; and (8) being able to provide informed written consent. Participants with congenital LSS, traumatic and pathological causes of LSS, symptomatic osteoarthritis (hip or knee) causing limited walking capacity, a neurological disease affecting walking capacity such as Parkinson, uncontrolled diabetes, heart failure, intermittent claudication of vascular origin, impaired cognitive capacity, and history of back or lower extremities surgery in the past 3 months will be excluded.

### Ethical considerations

This study will be conducted according to the Helsinki Declaration. The proposed study protocol received approval from the CIUSSS MCQ research ethics committee (CÉR-2023-649) and from the Human Research Ethics Board of UQTR which recognizes the ethics approval first received from the CIUSSS MCQ. Participants will be informed that they can withdraw at any moment during the study without having to provide an explanation and without negative consequences on their healthcare trajectory. Participants will be asked for permission from the research team to share relevant data with people from the universities taking part in the research or from regulatory authorities, when relevant. Also, it is important to note that if a participant is finally considered by a neurosurgeon for surgery, the proposed protocol will not interfere or delay the surgery. Participants randomized to the control group (education alone) will be offered the specific rehabilitation program after the completion of the study. Written informed consent will be obtained by all participants before completing the baseline assessment. This study does not involve the collection of biological specimens for storage.

### Randomization

All included participants will be randomized into one of the two groups (intervention or control) using a minimization method (allocation ratio of 1:1) to ensure that both groups will be balanced with respect to predetermined criteria. These minimization criteria have been identified based on factors known to have a negative influence on walking capacity and include smoking, diabetes, chronic obstructive pulmonary disease, and stroke. All criteria will have the same weight in the minimization process. Participants will be randomized using a computer-generated list of random numbers which will be placed into sealed and opaque envelopes numbered by an independent research assistant that is not involved in the selection, intervention, or assessment of participants. Each envelope will be opened in front of the participants at the end of the baseline assessment by another independent research assistant.

### Blinding

The researchers performing data collection as well as those performing statistical analyses will be blinded to the group allocation.

### Interventions

#### Intervention group

Participants allocated to the intervention group will receive a 6-week specific rehabilitation program which includes training and education sessions. The one-on-one training sessions will be composed of specific exercises to be performed 3 times per week under the supervision of a certified kinesiologist. Of the three training sessions, one will take place at UQTR’s outpatient clinic while the other two will take place online using a telecommunication platform (e.g., Zoom or Google Duo, depending on the participant’s preference) allowing for remote supervision of the training by the certified kinesiologist. Instructions regarding the selected telecommunication platform will be provided to the participants. Education will take place at week 2 and week 4 with the researcher responsible of the assessments. The presence to exercises and education sessions will be monitored by the responsible research team member (CT for exercises and MH for education).

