##### Education

Education will consist of two one-on-one sessions (during week 2 and week 4 assessments) during which participants will receive information directly related to LSS and NC using pre-recorded standardized videos developed for the study. This information consists of explanations of the pathophysiology of LSS and NC as well as expected natural history, usual symptoms, pain management strategies for daily living (body positioning when walking and when sleeping), and physical activity recommendations. Illustrations and videos will be used to enhance participants’ understanding and to ensure a standardized delivery of education. Participants will also be invited to ask questions. Each session will last for 20 min.

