#### Control croup

The participants in the control group will only receive the education sessions at week 2 and at week 4.

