### Data management

The researchers shall fill in data to the data collection sheet accurately, completely, and timely based on original observations. MH will be responsible to fill in data collection sheets during each evaluation, and CT will be responsible to fill in data collection sheets during each intervention. Researchers are responsible for ensuring the accuracy of all data entered and recorded. All data collected during this study are totally confidential and will never allow participant identification. Confidentiality will be assured by replacing the participants’ names by an alphanumeric code. The data collected will be stored under lock and key in the evaluation or intervention room (paper documents) or on a secure network with both network and electronic document access protected by passwords under the responsibility of the Chaire de recherche internationale en santé neuromusculosquelettique at the Université du Québec à Trois-Rivières. Only the research members will have access to these data. All of them have signed a confidentiality agreement. All data will be destroyed 5 years after the end of the study. For monitoring and control purposes, research files may be consulted by a person mandated by the CIUSSS MCQ Research Ethics Board or by a person mandated by authorized public agencies. All these persons and organizations adhere to a confidentiality policy. Full name, contact information, and the start and end date of participation for each participant in the project will be kept for 1 year after the end of the project in a separate directory maintained by the researcher responsible (MH) for this research project. For randomization purposes, a research assistant will have access to baseline data. This research assistant has also signed a confidentiality agreement.

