### Composition of the coordinating center and trial steering committee and plans for auditing trial conduct

The coordinator of the study is MH. She is responsible for all aspects of the local organization including identifying potential recruits and taking consent from participants. In addition to MH, CEC is responsible for the identification of potential recruits in the regional hospital outpatient clinic. CT (certified kinesiologist) is the supervisor of each session of exercises for the intervention group. The project is supervised by MD and AAM. Both are professors at UQTR and are supervising MH’s doctoral studies. The local Trial Steering Committee is composed of MH, CT, CEC, AAM, and MD. The team discussed the test protocols, the intervention content, and the related materials together. The committee will meet each month throughout the study. If there is any modification to the protocol that needs to be done or if there is any adverse event, the TSC will discuss the situation as soon as possible and will inform the research ethic committee. The monitoring will be conducted by the principal investigator of the study each month as an audit of trial conduct. There is no stakeholder and public involvement group for this study.

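### The plan declares its outcome assessors blinded, but the education, coordination and committee roles it gives to the assessing researcher put that blinding at serious risk

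*Protocol article*

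**What the plan says.** The Blinding section of the protocol article makes one unqualified statement: "The researchers performing data collection as well as those performing statistical analyses will be blinded to the group allocation".

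Other sections fix who does what:

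- **Intervention group:** "Education will take place at week 2 and week 4 with the researcher responsible of the assessments".
- **Education:** the sessions are one-to-one, last 20 minutes each, take place during the week 2 and week 4 assessment visits, and use pre-recorded videos. They cover pain management in daily life and physical activity, among other topics. "Participants will also be invited to ask questions".
- **Data management:** the same researcher, identified by initials, "will be responsible to fill in data collection sheets during each evaluation".
- **Composition of the coordinating center and trial steering committee:** this researcher coordinates the study, is in charge of its whole local organization, and is one of five committee members. The kinesiologist who supervises every exercise session is another. The committee meets monthly, and "if there is any adverse event, the TSC will discuss the situation as soon as possible".
- **Randomization:** "Each envelope will be opened in front of the participants at the end of the baseline assessment by another independent research assistant".

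**The concern.** Participants cannot be blinded to a supervised exercise program, so blinding the person who measures the outcome is a main safeguard against bias in measurement. The Blinding section claims that safeguard. The role assignments give the same person repeated occasions to learn the arm, and the article does not reconcile the two.

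This matters because of the primary outcome. In the Self-Paced Walking Test the participant sets the pace, and the test ends when symptoms make the participant stop for at least 3 s. A tester who knows the arm could affect the result by encouragement, or by deciding whether a stop was due to symptoms. If the two arms were treated differently in this respect, the difference would enter the treatment effect and could not be removed after data collection. The trial could also report assessor blinding that its own procedures do not support.

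**Working it through.** No figure in the plan bears on this point, so the check sets the sections side by side.

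1. **Is it one person?** The Intervention group section gives the education to the researcher responsible for the assessments and identifies by initials the person who monitors attendance at it. Data management and the committee section use the same initials for the person who fills in the evaluation sheets, coordinates the study and sits on the committee. One person therefore holds the roles of assessor, educator, coordinator and committee member.

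2. **Does anyone this person meets know the arm?** Yes. The envelope is opened in front of the participant at the end of baseline, so every participant knows the arm at all later visits. The kinesiologist also knows, because the supervised sessions are given only to the intervention group during the trial.

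3. **Where could allocation reach the assessor?**
   - *Education sessions.* Participants who know their arm, some of them exercising three times a week, are invited to ask questions in sessions that cover pain and physical activity. Disclosure is possible but not certain.
   - *Coordination.* A person in charge of all local organization would ordinarily be close to the running of the exercise program, which only one arm attends.
   - *Committee and adverse events.* The committee discusses any adverse event, and the Adverse events and harms section has each reported event discussed with the research team. An event that the kinesiologist brings from an exercise session can concern only an intervention-arm participant.

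4. **Which walking tests are exposed?** Table 1 schedules the test at baseline and at weeks 2, 4, 6 and 12. Baseline is protected, because the envelope is opened afterwards. The first education session falls at the week 2 visit, so the tests at weeks 4, 6 and 12 all follow it. Whether the week 2 test does so depends on the order within the visit, which the article does not give. The coordinator and committee routes are open at any time after baseline.

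5. **Can the size be computed?** No. That would need the spread of walking distance and the size of an assessor-induced shift. The Sample size section gives a target difference of 331 m but no standard deviation, and nothing in the article bears on the shift.

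6. **Staff time for the fix.** 66 participants × 2 sessions × 20 min = 2,640 min, and 2,640 / 60 = 44 hours. This is an upper bound, since it assumes that nobody drops out.

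**The case against.** The plan does contain real separations. Both arms receive the same education by the same videos at the same visits: "The participants in the control group will only receive the education sessions at week 2 and at week 4". Delivering it therefore does not tell the researcher which arm a participant is in. One independent assistant prepares the envelopes and another opens them. The kinesiologist, not the assessor, keeps the exercise attendance and intervention sheets. The walking test has an operational end-point, which limits the tester's discretion. A journal article may also leave to the full protocol any instruction to participants not to disclose, the order of events within a visit, and any masking of adverse-event discussion.

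Most of this stands, and it limits the point. A reader might infer that blinding is bound to fail, or that giving the education is itself unblinding. The documents support neither: no section shows allocation being disclosed in a session or at a meeting.

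The conflict in roles remains. Independent handling of envelopes protects concealment up to assignment, not blinding afterwards. Separate exercise sheets help less when the assessor also coordinates the trial and meets the kinesiologist on the committee. The 3 s rule leaves encouragement, and the attribution of the stop to symptoms, open to influence. The absence of detailed safeguards is not the complaint. The complaint is that roles stated in the article sit badly with a property claimed in the article.

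**Conclusion.** The point holds as a conflict between a stated property and stated roles: assessor blinding after baseline is at serious risk. The coordinator and committee roles are the strongest route, and the open question time with participants who know their arm adds to it.

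The conclusion rests on two inferences: that participants or the kinesiologist may reveal the arm in these contacts, and that a tester who knows it could affect a self-paced, symptom-limited walk. Both are plausible, and the documents prove neither. A reader might also want an inflated false-positive rate attached to this. Any such figure would rest on an assumed standard deviation and an assumed shift, so none is offered as a result.

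It should be settled before participants are assessed, because bias of this kind cannot be repaired in the analysis.

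**What to change.** - Have the independent research assistant who already opens the envelopes run the education videos and take the questions, after that visit's outcome tests are finished. The kinesiologist should not do this: it would put control participants in one-to-one sessions with the exercise provider and weaken the plan's stated aim of isolating the effect of the exercises.
- Keep the assessor out of exercise scheduling, and out of committee or adverse-event items that reveal allocation, until the last week 12 test.
- Ask participants not to disclose their arm to the assessor. Recording the assessor's guess of allocation is an optional extra.
- If the roles cannot be separated, change the Blinding section so that it no longer claims that the assessor is blinded after baseline.

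The cost is up to about 44 hours of existing staff time over the trial, plus some scheduling effort. It depends on that assistant being available, which the article does not state. Moving the education does not end the assessor's contact with participants at the visits, so the first change is not enough without the second and third.
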